### Evaluation of electromyography of masticatory muscles

2.9

The electrical activity resulting from the activation of the muscles will measured using the six-channel TMJOINT electromyograph (BTS Engineering) with an bioelectrical signal amplifier, wireless data transmission and disposable bipolar surface electrodes (Ag/AgCl, Medical Trace) measuring 10 mm in diameter. The EMG signal will be amplified with a 2000-fold gain and filtered within a frequency of 20 to 450 Hz. The impedance and common rejection mode ratio of the equipment are >1015 Ω/0.2 pF and 60/10 Hz 92 dB. The data will be collected and digitized at 1000 frames/second using the BTS MYOLA software program.

After cleaning the skin with 70% alcohol to diminish the impedance, the surface electrodes will be attached to the belly of the muscle in the region of greatest tone (determined with the volunteer performance moderate intercuspation). The inter-electrode distance will be 20 mm center to center, as recommended by the European Society Recommendations for Surface Electromyography (SENIAM). A reference electrode will be placed on the left wrist of the volunteer to impede the interference of external noise.

The muscles analyzed will be the masseter (right and left) and anterior temporal (right and left). Evaluations will be performed under 4 conditions:

(1)at rest,(2)during habitual maximum intercuspation with a strip of Parafilmbetween the molars to determine maximum voluntary contraction (MVC) of the muscles studied,(3)during habitual chewing (isotonic contraction) and (IV) during maximum intercuspation (isometric contraction) without parafilm. All readings will be performed 3 times with a two-minute rest period between readings. The collection time will be 15 seconds with the muscle at rest, 5 seconds during MVC and 10 seconds during isotonic and isometric contraction. A metronome set at 60 beats per minute will be used for the reading during habitual chewing.

The EMG signal collected during chewing will be rectified and normalized by the mean of the signal followed by the calculation of the root mean square (RMS) using a 500-ms moving window without overlap. The data will be normalized by the highest RMS obtained during MVC.

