There are limited studies related to disease management in children. Treatment involves the control of anxiety and sleep, psychotherapy, physical therapy, and medications. Considering the high prevalence and difficulty in resolving this condition due to the lack of established treatment, any knowledge about bruxism is important and can assist in establishing better assessment and treatment strategies. The goal of treatment is to reduce physical, muscular and psychological tension. Therefore, a multidisciplinary approach involving physical therapy, pharmacotherapy, dentistry and psychology is required.^[8,9]^

Acupuncture has also been successfully used for the treatment of bruxism, achieving a reduction in the activity of the masseter and anterior temporal muscles as well as a reduction of anxiety.^[10]^ The stimulation of particular acupoints can promote muscle relaxation, thereby alleviating muscle spasms, inflammation and pain. Moreover, such stimulation leads to the release of hormones, such as cortisol and endorphins, thereby promoting an analgesic effect.^[11]^ Acupuncture point stimulation can be achieved with the use of needles, laser or electric current.^[12]^

Low Intensity Laser Therapy is a noninvasive and inexpensive treatment. Trigger point irradiation is an effective treatment for orofacial pain as well as reduction of swelling and hyperemia.^[13]^ However, there are no studies reporting the result of applying low intensity laser therapy on acupoints in children with DS and bruxism.

The aim of the proposed study is to analyze salivary levels of dopamine and cortisol and muscle activity before and after treatment with low-level laser therapy administered to acupoints in children with DS.

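### The chewing EMG is divided by its own mean before MVC normalisation, so as written this one condition cannot show a change in chewing muscle activity

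*Protocol article*

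**What the plan says.** The Introduction of the protocol article gives the aim as "to analyze salivary levels of dopamine and cortisol and muscle activity before and after treatment". Section 2.4 places all evaluations before the first treatment and at the final session, so the EMG is a comparison of two visits.

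Section 2.9 describes surface EMG of the masseter and anterior temporal muscles under four conditions: rest, MVC with Parafilm, habitual chewing, and maximum intercuspation without Parafilm. Each reading is taken three times. For chewing, the processing is given as a sequence:

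1. "The EMG signal collected during chewing will be rectified and normalized by the mean of the signal"
2. "followed by the calculation of the root mean square (RMS) using a 500-ms moving window without overlap"
3. "The data will be normalized by the highest RMS obtained during MVC"

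The own-mean step is stated for the chewing signal only. Section 2.8 covers masseter activity during sleep separately, with the BiteStrip.

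**The concern.** EMG amplitude is usually made comparable across visits by dividing it by a reference contraction such as MVC. Section 2.9 puts another division first: the rectified chewing signal is divided by its own mean. For a rectified signal, the mean is the activity level. Dividing by it sets every chewing recording to a mean of 1, however hard the muscle worked, and the later division by MVC RMS acts on a number that no longer carries amplitude.

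At stake is whether one of the four EMG conditions can answer the question put to it. A true treatment effect on chewing activity would be invisible in this reading. A difference that did appear could come only from MVC or from burst shape, yet would be reported as chewing activity.

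**Working it through.** The article gives no numerical figure on this point to reproduce, so the check is algebra on the stated steps, followed by a simulation of them.

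**Inputs from section 2.9.** Sampling at 1000 per second; 10 s of chewing and 5 s of MVC; RMS in 500 ms windows without overlap; metronome at 60 per minute; order of steps as listed above.

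**Assumed inputs.** One half-sine burst per second on a 5% baseline; chewing scale 100 and MVC scale 200 in arbitrary units; outcome summarised as the mean of the window RMS values. The cancellation depends on none of these. Because the units are arbitrary, only ratios between results have meaning.

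**Algebra.** Write the chewing signal as g·x, where g is its amplitude, and let M be the highest MVC RMS.

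- As written: mean|g·x| = g·mean|x|, so the outcome is RMS(|g·x| / mean|g·x|) / M = RMS(|x| / mean|x|) / M. The factor g cancels.
- MVC normalisation alone: the outcome is g·RMS(x) / M. The factor g stays.

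The units agree with this. As written, the numerator has no units and the denominator is an amplitude, so the result is not a proportion of MVC.

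**Simulation, MVC held fixed.**

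| Chewing amplitude (relative) | As written | MVC normalisation only |
|---|---|---|
| 0.5 | 0.00661 | 0.096 |
| 0.7 | 0.00661 | 0.135 |
| 1.0 | 0.00661 | 0.193 |
| 1.3 | 0.00661 | 0.251 |
| 2.0 | 0.00661 | 0.386 |

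The as-written result does not move over a fourfold range of chewing amplitude. With MVC normalisation alone, a 30% fall in amplitude shows as a 30% fall (0.135/0.193 = 0.70). Averaging three readings does not help: the as-written mean is 0.00662 at relative amplitudes of both 0.7 and 1.0.

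**Chewing and MVC both 30% lower.** As written, only the denominator responds: 1/0.7 = 1.43, a rise of 43% (0.0066 to 0.0094). With MVC normalisation alone, 0.7/0.7 = 1, and the result stays at 0.193.

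**What else moves the as-written number.** Changing the burst shape, with amplitude scale and MVC fixed, took it from 0.0063 to 0.0074 over the shapes tried.

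**Other readings of the text.**

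- MVC signal also divided by its own mean: 1.047 at every chewing and MVC amplitude tried, so all amplitude is lost.
- Mean subtracted after rectification instead of divided: 0.100, 0.199 and 0.399 at relative amplitudes 0.5, 1 and 2, so amplitude survives.

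**The case against.** **It may be a wording slip.** The article is condensed and its English is uneven in places. Offset removal may have been meant, and under subtraction amplitude survives. This is a fair doubt about intent, but it does not rescue the text. Section 2.9 says the signal is normalised, mentions no subtraction, and joins the step to rectification, after which the mean is the activity level and not an offset. The 20 to 450 Hz filter also leaves little offset to remove. If subtraction was meant, the sentence still has to be corrected.

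**The two normalisations may be separate outputs.** The MVC sentence is not restricted to particular readings. If chewing were also reported as a percentage of MVC without the own-mean step, that version would keep amplitude. The article does not say so; it lists the steps in sequence.

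**The scope is narrow.** This stands. The own-mean step touches one of four EMG conditions. The article does not name chewing EMG as the primary outcome, and the Discussion looks to bruxism symptoms and cortisol.

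**Two further criticisms a reader might infer, which the documents do not support.**

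- That the own-mean step makes a fall in MVC alone look like a rise in chewing. With MVC 20% lower and chewing unchanged, the result rises by 25% (1/0.8), but it does so under any MVC-normalised measure, including the one recommended here. It is a reason to report MVC RMS, not a fault of this step.
- That half-second windows against "A metronome set at 60 beats per minute will be used for the reading during habitual chewing" make the result depend heavily on when recording starts. A large swing (mean window RMS from 49 to 70 units) needs square bursts filling exactly half of each cycle, silence between them, perfect timing and averaging over windows. The article states none of these. With 5% baseline activity, the range across start phases was 7% for 0.6 s bursts with perfect timing, 5 to 15% with 100 ms scatter around each beat, and about 1 to 2% when cycle lengths varied by 10%. Any such effect is noise unrelated to treatment arm.

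**Conclusion.** The point holds for the chewing condition as section 2.9 describes it. The loss of chewing amplitude is exact and rests only on reading the steps as divisions in the stated order; the simulated waveform is illustrative. Halving or doubling chewing activity changes the result by 0%, and a joint 30% fall in chewing and MVC appears as a 43% rise.

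A reader might infer that the trial cannot address muscle activity at all. The article does not support that: the rest, MVC and isometric readings are not described as divided by their own mean, and the BiteStrip is a separate measurement. Nor will the chewing number always stay still, since it can move through MVC or burst shape. A group difference in it would not, however, be evidence of a change in chewing activity.

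**What to change.** In section 2.9 and in the processing script:

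- Delete the normalisation of the chewing signal by its own mean. If offset removal was intended, state that the mean is subtracted before rectification.
- Express chewing RMS as a percentage of the highest MVC RMS of the same muscle at the same visit.
- Report MVC RMS as a result in its own right at both visits, so that a change in the denominator is visible.

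As an optional refinement, compute the chewing RMS over the whole 10 s recording or over whole chewing cycles in place of half-second windows.

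The cost is a change of wording and script. Recording procedures, visits and sample size are untouched, and signals already collected can be reprocessed as long as the raw recordings are kept. The change should be made before the EMG data are analysed.

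### Chewing EMG (section 2.9): read as division, normalising the rectified signal by its own mean cancels any uniform change in chewing amplitude, and the later MVC normalisation does not restore it

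*Protocol article*

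**What the plan says.** The stated aim in the Introduction includes "muscle activity before and after treatment with low-level laser therapy administered to acupoints". Section 2.9 records four muscles (right and left masseter, right and left anterior temporal) under four conditions. One is habitual chewing. Another is a clench on Parafilm, used "to determine maximum voluntary contraction (MVC) of the muscles studied".

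The processing paragraph of section 2.9 names chewing alone and sets the steps in this order:

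1. "The EMG signal collected during chewing will be rectified and normalized by the mean of the signal",
2. "followed by the calculation of the root mean square (RMS) using a 500-ms moving window without overlap",
3. "The data will be normalized by the highest RMS obtained during MVC".

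The text does not say whether the first normalisation divides or subtracts, or which recording supplies the mean. It does not mention offset removal or a mean carried over from the baseline visit. Section 2.4 places all evaluations before treatment and at the last session, so the chewing value is meant to be compared across two visits.

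**The concern.** Normalising by the signal's mean and normalising by MVC each put a recording on a relative scale. Here they are applied one after the other to the same data. Dividing a rectified signal by its own mean gives a signal whose mean is 1, however hard the child chewed. The RMS of that signal describes its shape (how peaked or intermittent it is), not the strength of contraction. Dividing by MVC afterwards cannot bring back what has been removed. It only adds dependence on clench strength.

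At stake is one component of the muscle-activity aim. If the laser uniformly reduced chewing activity, this outcome would show no change. If it reduced clench strength, the outcome would rise, and a reader would take that as stronger chewing.

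**Working it through.** The article gives no EMG figure to reproduce. The check is algebra, confirmed by a simulation.

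**Algebra.** Write the chewing signal as A·s(t) and the MVC signal as M·u(t), where A and M are amplitudes and s and u are fixed shapes. RMS is taken in 500-ms windows.

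- As written, with division by the own mean: Y = RMS(|A·s| / mean|A·s|) / max RMS(M·u) = [RMS(|s|) / mean|s|] / [M · max RMS(u)]. A cancels exactly, for any waveform. M stays in the denominator.
- Single normalisation (mean step dropped): Z = RMS(A·s) / max RMS(M·u) = (A/M) · RMS(s) / max RMS(u). This is chewing as a fraction of MVC.

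If chewing amplitude is multiplied by a and MVC by m, the ratio to baseline is 1/m as written and a/m with the single normalisation. For MVC down 20%, 1/m = 1/0.8 = 1.25, that is +25%.

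**Simulation inputs.** From section 2.9: "The data will be collected and digitized at 1000 frames/second"; "filtered within a frequency of 20 to 450 Hz"; 10 s of chewing and 5 s of MVC; a metronome at 60 beats per minute, taken as one chewing cycle per second; non-overlapping 500-ms windows. Assumed, because the article does not give them: chewing amplitude 60 and MVC amplitude 100 (arbitrary units), bursts filling 0.4 of each cycle, and a between-burst level of 0.1 of the burst level. The cancellation of A does not depend on these assumptions; the two burst-pattern rows do.

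**Results: ratio to baseline, mean over windows**

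| Change from baseline | As written (division by own mean, then MVC) | Single MVC normalisation |
|---|---|---|
| Chewing amplitude −30% | 1.000 | 0.700 |
| Chewing amplitude −50% | 1.000 | 0.500 |
| MVC −30%, chewing unchanged | 1.429 | 1.429 |
| MVC +30%, chewing unchanged | 0.769 | 0.769 |
| Chewing and MVC both −30% | 1.429 | 1.000 |
| Burst fraction 0.4 to 0.3 | 1.096 | 0.887 |
| Bursts −30%, between-burst level unchanged | 0.989 | 0.732 |

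The first two rows show the cancellation. The MVC-only rows are the same in both columns, because any percentage of MVC moves inversely with MVC. The difference is in the fifth row: when both contractions weaken by 30%, the as-written value rises 43%, while a true percentage of MVC stays at 1.000. In the sixth row, shorter bursts move the two measures in opposite directions.

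**Other readings of the sentence**

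- MVC signal also divided by its own mean: the result is 1.031 in every amplitude scenario tried. Neither chewing nor MVC amplitude is visible.
- Chewing not normalised by MVC at all: what is left is RMS(|s|)/mean|s|. A has still cancelled, and the inverse dependence on MVC does not arise.
- Mean subtracted after rectification: 0.700 and 0.500 for the 30% and 50% falls. Amplitude is kept, but the RMS is then taken about the mean of the rectified signal and is no longer the ordinary RMS of the EMG.
- Both visits divided by the baseline-visit mean: 0.700 and 0.500. Amplitude is kept.

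**The case against.** The strongest reply is that the sentence does not say divided, and does not say which recording the mean comes from. Subtraction, or a fixed baseline mean, would preserve amplitude fully, so the defect depends on one reading. This stands in part: the conclusion is conditional on division by the signal's own mean. But that is the natural meaning of the words, the alternatives are not in the article, and nothing elsewhere in it repairs the step. An analyst who follows the text literally removes the amplitude.

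A second reply is that the MVC sentence speaks of the data in general and may concern the other conditions rather than a second normalisation of chewing. That would remove the MVC artefact, but chewing amplitude would still have cancelled at the first step.

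A third reply concerns scope, and it stands. A reader might infer that this outcome cannot respond to any change in muscle activity, or that the trial's muscle-activity aim is lost. The documents support neither. The value still moves with MVC and with burst pattern, so it is misleading rather than inert. The mean step is stated for chewing only. The rest and isometric readings in section 2.9 and the BiteStrip recording during sleep in section 2.8 are separate measures that this step does not touch, and the article does not name chewing EMG as the primary outcome.

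Nor is this merely a detail left to a fuller document: the article fixes the order of the steps itself.

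**Conclusion.** The point holds for the chewing EMG, conditional on reading the mean normalisation as division by the signal's own mean. On that reading a uniform change in chewing amplitude has exactly no effect on the outcome (1.000 for a 30% or 50% fall, against 0.700 or 0.500 without the step). If MVC normalisation follows with MVC in its original units, the value varies as 1/MVC (+25% for MVC down 20%), and it moves somewhat with burst pattern (1.096 and 0.989 in the two cases tried, under the assumed burst settings). The chewing result in all four muscles is affected; the other muscle-activity measures are not.

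Two further inferences go beyond the documents. A loss of power could be put in figures only by assuming a treatment effect and between-child SDs, none of which the article gives; such a figure would be illustrative, and the exact cancellation does not need it. It also cannot be taken for granted that children already recorded can be reprocessed: the article says that EMG data are collected and digitised, but not that raw signals are kept.

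**What to change.** In section 2.9:

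- Delete the normalisation by the mean of the signal.
- Remove any offset from the raw signal before rectification.
- Compute RMS in non-overlapping 500-ms windows, as now.
- Normalise once, as a percentage of the highest MVC RMS, with the MVC signal processed by the same steps.

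If mean subtraction was what was meant, say so and place it before rectification. Reporting the un-normalised RMS alongside is optional; it would help to separate a change in chewing from a change in MVC, since a percentage of MVC also moves when MVC moves.

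The cost is one sentence and one processing setting, with no extra visits or recordings for children still to be assessed. For any child already recorded, the correction depends on whether the raw signals were kept; this should be confirmed before the text is changed.

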### Allocation

2.10

The participants will be randomized to two groups with the aid of a randomization site (randomization.com): Group A – active photobiomodulation(n = 15); Group B – sham photobiomodulation(n = 15).

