**Methods::**

A randomized, controlled, clinical trial will be conducted. Individuals 4 to 17 years of age with a diagnosis of DS and possible sleep bruxism will be screened at the Integrated Health Clinic of Nove de Julho University. We will evaluate orofacial dysfunction (Nordic Orofacial Test - Screening questionnaire), Masseter muscle activity during sleep will be assessed by BiteStrip and the masticatory muscles will be evaluated by electromyography (BTS TMJOINT) head posture as well as salivary cortisol and dopamine. After the evaluations, the participants will be randomized into 2 groups: Grupo 1 – treatment with low-level laser therapy at a wavelength of 808 nm; Group 2 – sham treatment (simulated laser therapy). Treatment will be conducted twice per week for a total of 12 sessions. The data will be tabulated and treated using GraphPad Prism version 7.0. The Kolmogorov-Smirnov test will be used to determine the normality of the data. Variables that fit the Gaussian curve will be expressed as mean and standard deviation. The ANOVA 2-way will be used for comparisons between the groups, with the significance level set to 5% (*P* < .05).

**ClinicalTrials registration number:** NCT04211870.

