## Introduction

1

Down syndrome (DS) is genetically characterized by the total or partial presence of an extra chromosome in par 21, also known as chromosome 21 trisomy. One of the manifestations found in individuals with DS is the muscular hypotonia, especially of the masticatory and oropharyngeal muscles. Such muscles may compromise basic actions such as swallowing, breathing and speech.^[1]^ Therefore, they may present alterations in oral functions, such as delayed eruption of deciduous dentition, open or crossbite, microdontia, macroglossia and reduced oral cavity, providing oral breathing and salivary leak.^[2]^

Hypotonia, muscle weakness, sluggish motor response information, and sensory changes can impair their ability to maintain adequate muscle balance. Consequently, the movements become difficult, slow and disorganized, resulting in stress, anxiety and consequently poor quality of life. In addition, due to muscle hypotonia, children with DS tend to project their tongue, and for more stable occlusion they also project their jaw. Associated, these factors may cause mouth breathing due to mouth opening, potentially causing sleep disturbance, Obstructive Sleep Apnea syndrome, and bruxism.^[3,4]^

Bruxism is defined by masticatory muscle activities that occur during sleep (characterized as rhythmic or non-rhythmic) and wakefulness (characterized by repetitive or sustained tooth contact and/or by bracing or thrusting of the mandible).^[5]^

Ethylogy is multifactorial and the main risk factors related to bruxism are gender, age, gene, mixed position, a lot of moving during sleep, sleeping with open mouth, snoring loudly, sleeping hours, sleeping anxiety, nervousness, passive smoking, high psychological reactions. with light on, cheek tone, emotional symptoms, mental health problems, birth weight, hyperactivity.^[6]^ In individuals with DS bruxism is often associated with sleep problems, snoring and obstructive sleep apnea.^[1]^

Stress has been reported to increase hypothalamus-pituitary-adrenal axis activity and alter the pattern of cortisol secretion, an important hormone used as a biomarker of psychological stress. Free cortisol determination can be easily measured in saliva. Stress sensitivity, as assessed by salivary cortisol, may be a psychological factor associated with bruxism.^[7]^

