#### Inclusion criteria

2.3.1

(1)Children and adolescents with a diagnosis of DS(2)Four to seventeenyears of age(3)Bruxism, based on parental reports of the occurrence of grinding the teeth, incisal and/or occlusal and the questionnaire for the evaluation of bruxism

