### Statistical analysis

2.12

The data will be tabulated and treated using GraphPad PRISM version 7.0. The Kolmogorov-Smirnov test will be used to determine the normality of the data. Variables that fit the Gaussian curve will be expressed as mean and standard deviation. The ANOVA two-way will be used for comparisons between the groups, with the significance level set to 5% (*P* < .05). by one of the authors ([name], Applied Statistics Specialist).

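### With 15 children per arm aged 4 to 17, prespecify age as a covariate: a cheap guard against a chance age gap, not the repair of an invalid test

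*Protocol article*

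**What the plan says.** The inclusion criteria (2.3.1) admit children at "Four to seventeenyears of age". Section 2.10 describes allocation in one sentence: "The participants will be randomized to two groups with the aid of a randomization site (randomization.com"), followed by the group sizes, "Group A – active photobiomodulation(n = 15); Group B – sham photobiomodulation(n = 15"). It names no stratification factor and does not say whether the list is stratified. The abstract places allocation after the assessments: "After the evaluations, the participants will be randomized into 2 groups". Each child's age is therefore known before allocation.

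The Introduction states that "the main risk factors related to bruxism are gender, age" and then a long list of others. Section 2.4 sets all evaluations before treatment and at the last session. Section 2.12 fixes the method: "The ANOVA two-way will be used for comparisons between the groups", at the 5% level. The two factors of that ANOVA are not named, and neither is any covariate.

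**The concern.** The age range runs from preschool to late adolescence, and the arms are small. Randomisation balances age over many hypothetical trials, but only one will be run, and with 15 per arm its mean ages can differ by two years or more by chance. If age predicts an outcome at the last session, or predicts how the outcome changes over six weeks, such a gap moves the between-arm difference in that trial. Age would also sit in the error term and cost some precision.

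The EMG and NOT-S assessments are where an age effect on change is easiest to imagine. They depend on a child performing tasks such as a maximal clench or chewing to a metronome, and EMG is normalised to the clench. Adding age after a gap has been seen would look data-driven, so the decision is worth making beforehand.

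**Working it through.** **Inputs from the article.** n = 15 per arm (2.10); ages 4 to 17 years (2.3.1); significance level 5% (2.12); measurements before treatment and at the last session (2.4).

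**Assumed inputs.** Two-sided testing. Ages either uniform from 4 to just under 18, SD = 14/√12 = 4.04 years, or normal with SD 3 years. Age-outcome correlation r of 0, 0.3, 0.5 or 0.7. The article gives neither an age distribution nor a correlation.

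**The plan's own figure.** The article states 15 per arm without an effect size, SD or power, so there is nothing to reproduce. For scale, a two-sided 5% t test with 15 per arm has 80% power for a difference of 1.06 SD.

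**Step 1: size of a chance age gap.** SE of the gap = SD × √(1/15 + 1/15) = SD × 0.365.

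| Assumed ages | SE of gap | P(gap > 2 years) | P(gap > 3 years) |
|---|---|---|---|
| Uniform, SD 4.04 | 4.04 × 0.365 = 1.48 years | P(\|Z\| > 2/1.48), about 17% to 18% | about 4% |
| Normal, SD 3 | 3 × 0.365 = 1.10 years | P(\|Z\| > 2/1.10), about 7% | 0.6% |

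Simulation of 100,000 allocations gave the same values. In SD units the choice of distribution hardly matters: P(gap > 0.5 SD) = P(|Z| > 0.5/0.365), about 17%.

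**Step 2: effect on a comparison of last-session values with no covariates.** The shift is r × gap in SD units. For a 0.5 SD gap (about 2 years under uniform ages) it is 0.3 × 0.5 = 0.15, 0.5 × 0.5 = 0.25 and 0.7 × 0.5 = 0.35 outcome SD. Simulated rejection rates (40,000 trials per setting):

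| r | False positives, all trials, unadjusted | False positives when gap ≥ 0.5 SD, unadjusted | Same, with age term | Power at 1.06 SD, unadjusted → age term |
|---|---|---|---|---|
| 0 | 5.1% | 4.6% | 4.8% | 80% → 79% |
| 0.3 | 5.0% | 7.4% | 4.7% | 80% → 82% |
| 0.5 | 4.9% | 11.4% | 5.2% | 80% → 88% |
| 0.7 | 4.9% | 17.9% | 5.1% | 80% → 97% |

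The overall error rate is correct without adjustment. Only the rate conditional on a large gap is not.

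**Step 3: if the ANOVA factors are group and time.** A stable age effect enters both measurements and drops out of the group-by-time contrast. At r = 0.5 with a 0.5 SD gap the simulated shift was -0.006 SD, and rejection was 5.1% both overall and in trials with a large gap. The group main effect of the same ANOVA averages the two times and does carry the gap. Section 2.12 does not say which term is the test.

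**Step 4: what age adds once baseline is in the model.** With an assumed pre-post correlation of 0.6, adding age to a model that already holds the outcome's baseline value moved power by about -1.5 to +2.4 points. The gains in Step 2 are therefore an upper picture. A strong age effect that baseline does not capture would bring more.

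**The case against.** The strongest case against has four parts.

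First, the article is condensed. It does not say the list is unstratified, and stratification and covariates are commonly set out in the full protocol or SAP. This stands for allocation, which is why stratification is only an option below. It is weaker for the analysis, because section 2.12 names a specific method, and age in years has no place in a two-way ANOVA of group and time.

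Second, the Introduction ties age to the risk of having bruxism, which every participant is already taken to have. It does not tie age to cortisol, dopamine, EMG or six-week change, and it lists gender alongside age. This stands. A reader might infer that the protocol itself calls age a strong predictor of its outcomes; it does not, so every shift above rests on an assumed correlation. Age is singled out here because its eligible range is so wide.

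Third, outcomes are measured before and after, so a stable age effect may cancel. This stands for the interaction term, but not for the group main effect or for an age effect on change. The exclusion of children who cannot understand the evaluations limits the latter without equalising task performance across ages.

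Fourth, randomisation already gives valid inference. This stands too. A reader might conclude that the unadjusted test is biased or its error rate inflated, but over all allocations the rate is 4.9% to 5.1%. Nor would a chance gap be beyond repair, since a prespecified age term handles it even with the list unchanged.

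**Conclusion.** The point holds as a small, inexpensive improvement to a stated analysis. A gap in mean age above 2 years has a probability of about 7% (age SD 3) to 17% (uniform ages), and gaps of that order matter only if age predicts the last-session level or the change. On an unadjusted last-session comparison, a 0.5 SD gap would be worth 0.15 to 0.35 SD at correlations of 0.3 to 0.7. On a group-by-time contrast with a stable age effect it would be worth nothing. Once baseline is in the model, the expected change in power from adding age is a point or two in either direction. The main value is protection in the one trial actually run. The age distribution, the correlations and the pre-post correlation are all assumptions. The documents do not support calling the design or the test wrong.

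**What to change.** In 2.12, for the continuous outcomes (cortisol, dopamine, EMG), compare arms on the last-session value by a linear model with treatment group, the outcome's baseline value and age in years, all prespecified. For the four-category BiteStrip score, use an ordinal model with the same covariates. The plan should also say which model carries the 0-to-12 NOT-S total.

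If the list has not been generated, section 2.10 could optionally use permuted blocks within two age bands. A split at 11 years is one choice, although nothing in the article dictates that cut. With perfect balance within two 7-year bands of uniform ages, the SE of the gap would fall from 1.48 to (7/√12) × 0.365 = 0.74 years; incomplete blocks would give back a little of this. If enrolment has begun, keep the list and add only the covariate.

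Cost: no new data, because age is already held. The age term uses one degree of freedom, about 1 to 2 points of power if age is unrelated to the outcome. Two age bands need a second list and may leave the arms one or two off 15/15. With 30 children, two bands are as many as the sample can reasonably carry, and sparse BiteStrip categories may have to be merged by a rule set in advance.
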